### Study population

#### Sample size calculation

Sample size estimation was based on the NOTABLE cohort study [24]. Previous studies report a conversion rate for vNOTES in tubal ectopic pregnancies between 1.83% and 3.07%, suggesting a surgical success rate of approximately 95%.^34,35^A one-sided non-inferiority test was used to determine the sample size, assuming that vNOTES would remain a preferred option despite a potential 15% lower success rate compared to TU-LESS, which results in visible scarring. To achieve 85% power for non-inferiority with a 95% expected success rate in both groups, a total of 54 cases were required. Accounting for an anticipated 20% dropout rate, the final sample size was set at 72 participants, with 36 per group.

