### Perioperative assessment and short-term postoperative outcomes

#### Primary short-term outcome

Completion of surgery using the allocated technique is Primary short-term outcome that we will focus on. We will also conduct a detailed analysis of cases requiring surgical conversion, including the reasons for conversion, the type of surgical techniques converted into, as well as the specific complications and their severity.

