### Statistical analysis

Statistical analyses will be conducted using SPSS (Version 25.0) and R. Continuous variables will be analyzed using t-tests or Mann–Whitney tests, with results presented as means ± standard deviations for normally distributed data and medians with interquartile ranges for non-normally distributed data. Categorical variables will be analyzed using chi-square or Fisher’s exact tests. To mitigate bias, statistical techniques such as propensity score matching (PSM), stratification, multivariate analysis, Cox regression, and generalized estimating equations (GEE) will be employed as necessary. A binary logistic regression analysis will also be conducted to assess the risk factors for surgical conversion, incorporating variables that demonstrate a significant statistical difference in the univariate comparisons. Statistical significance will be set at *p* < 0.05.

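### On the plan's own inputs, 54 evaluable patients give about 81% power at one-sided 5%, not 85%, and 20% dropout turns 54 into 68, not 72

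*Protocol article*

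**What the plan says.** The calculation is in the protocol article under Sample size calculation. The design is given as "A one-sided non-inferiority test was used to determine the sample size". The margin is implied by the statement that vNOTES would still be preferred "despite a potential 15% lower success rate compared to TU-LESS". The power and evaluable number follow: "To achieve 85% power for non-inferiority with a 95% expected success rate in both groups, a total of 54 cases were required". The last step is the inflation: "Accounting for an anticipated 20% dropout rate, the final sample size was set at 72 participants, with 36 per group".

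The success rate in this calculation matches the outcome under Primary short-term outcome: "Completion of surgery using the allocated technique is Primary short-term outcome". No alpha is attached to the calculation. The only level in the article is the general one under Statistical analysis: "Statistical significance will be set at *p* < 0.05".

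**The concern.** Every input except alpha is printed, so the two outputs can be checked. Neither 54 nor 72 comes out. The 54 matches a lower power than the one claimed, and the 72 matches a higher dropout rate than the one claimed.

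This is the article's only sample size justification. Readers and an ethics committee would take 85% power and 20% loss as properties of the design, and the two cannot both hold with 54 evaluable and 72 randomised. A fuller protocol or analysis plan could supply the missing alpha, but neither conventional one-sided alpha, 5% or 2.5%, makes 54 agree with 85%, and alpha plays no part in the dropout step.

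**Working it through.** **Inputs** (all from Sample size calculation unless noted)
- Success 0.95 in both arms, so the true difference is 0.
- Margin 0.15, read as absolute percentage points.
- One-sided test, 85% power, 1:1 allocation.
- Alpha: not stated for this calculation. One-sided 0.05 is the lenient reading of the general level under Statistical analysis. One-sided 0.025 is an assumption, shown for range.

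**Step 1: where 54 comes from.** The unpooled normal-approximation formula is

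n per arm = (z_α + z_β)² × 2 × 0.95 × 0.05 / 0.15² = (z_α + z_β)² × 0.095 / 0.0225

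| One-sided α | Power | n per arm | Rounded | Total |
|---|---|---|---|---|
| 0.05 | 80% | 26.1 | 27 | **54** |
| 0.05 | 85% | 30.4 | 31 | **62** |
| 0.025 | 80% | 33.1 | 34 | 68 |
| 0.025 | 85% | 37.9 | 38 | **76** |

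The plan's 54 is reproduced exactly, but as the answer for 80% power at one-sided 5%.

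**Step 2: power with 27 per arm.** Power = Φ(0.15 / √(0.095/n) − z_α). With n = 27, 0.15 / √(0.095/27) = 2.529.
- One-sided 5%: Φ(2.529 − 1.645) = Φ(0.884) = 81%.
- One-sided 2.5%: Φ(2.529 − 1.960) = Φ(0.569) = 72%.
- Alpha needed for 85%: 1 − Φ(2.529 − 1.036) = 6.8% one-sided, looser than any level in the article.

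**Step 3: other formulas.** At one-sided 5% and 85% power, the continuity-corrected formula needs 43 per arm, the Farrington-Manning formula 45 and the arcsine formula 64. All lie further from 27. Using the cited conversion rates directly (1.83% to 3.07%, so success of 98.17% to 96.93%) gives totals of 24 to 40 at one-sided 5% and 30 to 48 at 2.5%. These do not give 54 either.

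**Step 4: the dropout step.**
- 54 / (1 − 0.20) = 67.5, so 68 (34 per arm).
- The common shortcut, 54 × 1.2 = 64.8, gives 65 (33 per arm).
- 54 / 72 = 0.75, so 72 is what 25% dropout gives.

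**Step 5: what 72 delivers, same formula.**

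| Evaluable | Per arm | One-sided 5% | One-sided 2.5% |
|---|---|---|---|
| 72 × 0.80 = 57.6 | 28.8 | 83% | 74% |
| 72 | 36 | 90% | 83% |

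**Step 6: cost of keeping both stated figures.** 62 / 0.80 = 77.5, so 78 randomised at one-sided 5%. 76 / 0.80 = 95, so 96 for equal arms at one-sided 2.5%.

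**The case against.** The best defence is that the two slips work against each other. The inflation step errs towards more patients: 72 exceeds the 68 that the plan's own 54 and 20% require. At one-sided 5%, 72 less 20% leaves power of 83.3%, only 1.7 points below the claim. If everyone is evaluable, which is plausible for an outcome known at surgery, power is about 90%, above the claim. The larger deficits all come from one-sided 2.5%, which the article does not state. This stands, and it limits the size of the point. It does not make either printed step correct.

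Three stronger readings are tempting, and the documents do not support them.

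- *That the trial is too small at 72.* This holds only under an assumed one-sided 2.5%, or if both 85% power and 20% loss are treated as binding.
- *That the dropout allowance should be removed because completion of surgery is known in theatre.* Patients can withdraw between randomisation and surgery. Study design and Primary long-term outcomes also name pregnancy, vaginal delivery and wound complications among the primary outcomes, and there a loss over years is relevant. An allowance is cautious, not an error; what is missing is which outcome it serves.
- *That true power is lower because the normal approximation is poor near 95% success.* Exact enumeration at 36 per arm gives about 79% power at one-sided 5% and 65% at 2.5% with a score (Farrington-Manning) bound. The article names no non-inferiority interval, and an analysis plan may properly fix it. These figures matter only if such a bound is the chosen test; they do not show that the paragraph is miscalculated.

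**Conclusion.** Wrong as written, on two counts. The evaluable number and the power disagree: 54 gives about 81% at one-sided 5% (72% at 2.5%), while 85% needs 62 (76). The dropout rate and the final number disagree: 20% gives 68, and 72 means 25%.

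The practical effect is modest. At one-sided 5% the 72 patients have about 83% power after the stated loss and about 90% without loss. At one-sided 2.5% the figures are 74% and 83%, so 85% is missed either way. These results assume an absolute 15-point margin, equal arms, a true success rate of 95% in both, and the normal-approximation formula. The finding that both steps fail does not depend on which of the two alphas was meant.

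**What to change.** Keep 72 randomised (36 per group) and correct the paragraph so that power, evaluable number and dropout agree under one method and one stated one-sided alpha. At one-sided 5% by the normal approximation, for example, it could say that 54 evaluable patients give about 81% power, and that 72 randomised give about 83% after a 20% loss and about 90% if all are evaluable. State which outcome the 20% allowance is for.

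If the non-inferiority test will use a score or Newcombe bound, report every power on that basis instead, without mixing the two methods. For 36 per arm that is about 79% at one-sided 5% or 65% at 2.5%.

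The change is to wording only and needs no extra patients. The price is a less favourable claim: 85% can no longer be stated once the 20% loss is allowed for. A sponsor who wants to keep both 85% and 20% would need 78 randomised at one-sided 5%, or about 96 at 2.5%, by the planning formula.

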### Patient selection

#### Inclusion criteria

Diagnosis of tubal ectopic pregnancy.Sign informed consent.Age ≥ 18 years.Indications for laparoscopy.

#### Exclusion criteria

No history of sexual activity.Suspected pelvic infection.Vaginal stenosis or vaginitis.Severe pelvic adhesions.History of hernia or rectal surgery.

### Study interventions

Both vNOTES and TU-LESS procedures will follow standardized surgical techniques described in previous literature [34, 35]. All procedures will be performed by a team of experienced gynecologic endoscopic specialists. Among them, 10 surgeons have over 20 years of experience, each performing more than 100 TU-LESS and 50 vNOTES procedures annually, while the remaining 10 surgeons have over 10 years of experience, performing 50–100 TU-LESS and 25 vNOTES cases per year. All surgeons have completed their learning curves.

### Recruitment procedures and follow-up plan

#### Recruitment

The enrolment flowchart and follow-up plan for the vNOTESTEP study are presented in Figs. 1 and 2. Three trained cohort coordinators (CCs) will provide standardized vNOTES and TULESS-related information to potential participants, outlining study requirements, including multiple follow-up visits and questionnaire completion. Patients will be enrolled upon signing informed consent, after which baseline data will be collected from the Hospital Information System (HIS).

#### Perioperative management

A preoperative assessment will determine the appropriate surgical approach. Intraoperative and short-term postoperative data will be recorded in the HIS. Preoperative Female Sexual Function Index (FSFI) and postoperative Visual Analog Scale (VAS) scores will also be collected. WeChat groups will be established for patient education, management, and follow-up, with patients invited to join before hospital discharge.

#### Postoperative follow-up

A total of eight follow-up visits will be conducted over four years at 1, 3, and 6 months, and annually from years 1 to 4. Standardized questionnaires and clinical assessments will be administered as presented in Fig. 2. Completed questionnaires will be automatically uploaded to the study database. Ultrasound and gynecologic physical examinations will be performed when necessary.

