## Methods

### Study design

The vNOTESTEP study is a single-blind RCT designed to evaluate the perioperative and long-term postoperative outcomes of vNOTES compared withTU-LESS in patients with tubal ectopic pregnancy. Considering ethical concerns and the low likelihood that patients would be unaware of their incision site, this study will adopt a single-blind design, with blinding applied only to the outcome assessors (OAs) and not to the patients. After obtaining informed consent from each participant, preoperative assessments will be conducted. Following randomization, salpingectomy will be performed via either vNOTES or TU-LESS approach. The primary outcomes include perioperative outcomes like surgical conversion, change of postoperative sexual function, pregnancy, and vaginal delivery. The study will be conducted at CWCCH, a university teaching hospital and regional training center for vNOTES, spanning from 2024 to 2030, with two years allocated for recruitment and three to five years for follow-up.

CWCCH has a highly experienced team of approximately 20 gynecologic endoscopic specialists, who collectively perform 500–600 vNOTES and 1000–2000 TU-LESS procedures annually. Randomization and grouping will be performed by a cohort manager (CM) using a computer-generated system after stratification. To maintain blinding, identifiable patient information will be removed. Outcome assessors (OAs) will be blinded to patient allocation, with OA1 responsible for evaluating incisional wounds and OA2 assessing non-incisional wound-related perioperative and postoperative outcomes. Both the umbilical and vaginal incisional sites will be dressed uniformly to achieve blinding during hospitalization. Patients will not be informed of the type of surgery they undergo either preoperatively or postoperatively to maintain blinding as much as possible. In cases of severe incisional complications, blinding may be lifted for appropriate medical intervention. Information exchange between CM, OAs, and cohort coordinators (CCs) will be restricted until the study’s completion.

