**Body Image Questionnaire (BIQ)**: An eight-item scale assessing postoperative body image and cosmetic perception. Items 1–5 evaluate patients’ self-perception and satisfaction with their appearance, while items 6–8 assess satisfaction with the surgical scar [36, 37]. BIQ will be administered at the 1-month follow-up visit.**Visual Analog Scale (VAS)**: A validated tool for pain assessment, consisting of a 10 cm-long scale ranging from ‘no pain’ to ‘extreme pain.’ Patients will indicate pain intensity on postoperative days 1, 2, and 3. Pain scores will be classified as: <1 cm (painless), 1–3 cm (mild), 4–6 cm (moderate), and 7–10 cm (severe). CCs will record and upload VAS scores to the study database.**Female Sexual Function Index (FSFI)**: A validated 19-item scale assessing six domains of sexual function, including libido, arousal, lubrication, orgasm, satisfaction, and pain [38]. A total score < 26.5 indicates impaired sexual function [39]. The FSFI will be administered preoperatively and postoperatively at 3 and 6 months. Since sexual activity is contraindicated for one month following vNOTES to allow vaginal incision healing, FSFI will not be assessed at earlier time points [40]. **Pregnancy and delivery outcomes**: A self-designed **Pregnancy and Delivery Questionnaire (PDQ)** collecting postoperative gestational history (see Appendix 1). The PDQ includes seven questions regarding pregnancy status, conception method, delivery mode, parity, vaginal laceration, and incisional hernia (IH). This will be administered at all follow-up visits except the 1st month. Patients will be encouraged to undergo pregnancy monitoring and delivery at CWCCH to facilitate comprehensive data collection via HIS.**Incisional complications**: At each follow-up visit, patients will undergo gynecologic physical examinations to assess for IH. Patients with suspected IH (i.e., those experiencing incisional pain or a bulge) will be referred for imaging investigations, including ultrasound, computed tomography (CT), or magnetic resonance imaging (MRI). Diagnosed IH cases will be treated appropriately, and CCs will document relevant findings in the study database.

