### Long-term postoperative outcomes

#### Primary long-term outcomes

Pregnancy and vaginal delivery outcomes and incidence of incisional wound complications.

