#### Secondary long-term outcomes

Cosmetic satisfaction, impact on sexual function, pregnancy outcomes, and IH occurrence. These outcomes will be evaluated according to the follow-up schedule outlined in Figs. 1 and 2.

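### The protocol makes the follow-up examination for incisional hernia both universal and discretionary, and claims blinding for an assessor who evaluates the incision

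*Protocol article*

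**What the plan says.** **Examination.** Two sections of the protocol article set the rule for physical examination after discharge.

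- Postoperative follow-up: "Ultrasound and gynecologic physical examinations will be performed when necessary". No criterion for necessity is given.
- Items of follow-up visits, under incisional complications: "At each follow-up visit, patients will undergo gynecologic physical examinations to assess for IH". Imaging is conditional there: "Patients with suspected IH (i.e., those experiencing incisional pain or a bulge) will be referred for imaging investigations".

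**Outcome status.** The primary long-term outcomes are "Pregnancy and vaginal delivery outcomes and incidence of incisional wound complications". The secondary long-term outcomes are "Cosmetic satisfaction, impact on sexual function, pregnancy outcomes, and IH occurrence". IH therefore falls within the subject of a primary outcome and is also named as a secondary one.

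**Blinding.** Study design describes a single-blind trial, with "blinding applied only to the outcome assessors (OAs) and not to the patients". There are two assessors, "with OA1 responsible for evaluating incisional wounds", while OA2 takes the outcomes that do not concern the incision. Both incision sites are to carry the same dressing during the hospital stay. Data collection and management adds that assessors stay blinded and that the surgical approach is concealed before the coordinators collect perioperative and follow-up data.

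**The concern.** An incisional outcome can be compared fairly only if both arms are searched for it in the same way. A universal examination does that. An examination left to need depends on what the patient reports and what the clinician suspects. Here the incisions are at different sites, umbilical and vaginal, so there is no assurance that the prompts to examine would arise equally often in the two arms.

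The second matter is the blinding claim. If the assessor of the incision can tell the arm from its site, a report of blinded outcome assessment would be inaccurate for exactly the outcome most exposed to the assessor's expectations.

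**Working it through.** The plan states no figure on this point, so the check is mainly a comparison of its statements.

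**1. Can the two examination rules both hold?**

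| Procedure | Postoperative follow-up | Items of follow-up visits | Compatible? |
|---|---|---|---|
| Ultrasound or other imaging | As needed | If pain or a bulge raises suspicion | Yes |
| Physical examination | As needed | Every visit | No |

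The conflict is confined to the physical examination. If the discretionary rule governed, two routes to an IH diagnosis would remain: the hernia item in the pregnancy and delivery questionnaire (given at every visit except month 1) and imaging prompted by symptoms or signs. The first rests on patient report. The second rests on patient report or on an examination that might not take place.

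**2. Which outcome is affected?** The every-visit examination is specifically for IH. It is described under incisional complications, and the primary long-term outcome is the incidence of incisional wound complications. The secondary list names IH separately. The conflict therefore bears on a primary outcome through its hernia component, and on a named secondary outcome directly.

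**3. Does the described concealment support assessor blinding for the incision?** The site of the incision is the allocation. Dressing both sites alike can hide this while the dressings are on, and the article limits that measure to the hospital stay. Concealing the surgical approach in the data handled by the coordinators does not hide a wound or scar from someone examining it. The article does not say who performs the follow-up examinations. This does not matter for the argument, because anyone who inspects the site sees the same thing.

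**4. Scale, TU-LESS arm only.** Inputs: IH incidence of 5–7% for TU-LESS (Discussion); 36 patients per group and 20% anticipated dropout (Sample size calculation).

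- Patients remaining: 36 × (1 − 0.20) = 28.8, taken as 29.
- Expected cases, low end: 29 × 0.05 = 1.45. High end: 36 × 0.07 = 2.52. That is about 1.5 to 2.5.
- Effect of one case on the arm's rate: 1/36 = 2.8 points; 1/29 = 3.4 points.

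The article gives no figure for how much detection would fall under discretionary examination. Assume it falls to between 75% and 50% of what an every-visit examination finds. The observed rate in this arm would then be lower by between 5% × (1 − 0.75) = 1.25 points and 7% × (1 − 0.50) = 3.5 points. With 36 patients that is 36 × 0.0125 = 0.45 to 36 × 0.035 = 1.26 cases. Imperfect detection of this order is worth about one case, which is a large part of what the arm is expected to yield.

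**The case against.** The best defence of the examination rule is that the section on incisional complications is the specific one and the other sentence is a general remark. On that reading the specific rule governs and no harm follows. The schedule figure, which is not available here, may also show which rule is meant. This narrows the point to a repair of wording. It does not remove it: no schedule can make both sentences true, and nothing in the text says which prevails.

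It is also fair to say that the effect of one case reflects the small arm, not ascertainment bias, and that the Discussion already concedes the sample may be too small for rare complications. The numbers above show sensitivity to how cases are found. They do not estimate a bias.

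A reader might infer more than the documents support:

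- **That the patient-blinding statements contradict each other.** Study design says patients are not blinded and also that "Patients will not be informed of the type of surgery they undergo either preoperatively or postoperatively". Withholding the information without claiming formal patient blinding is coherent, and the Discussion explains the choice and admits that the umbilical incision may compromise it.
- **That vaginal hernias would be under-detected because patients notice an umbilical bulge more easily.** The article does not say so. Neither the direction nor the presence of differential detection is established.
- **That 1.5 to 2.5 hernias are expected in each arm.** The quoted rate is for TU-LESS, and the Discussion says those findings do not carry over directly to vNOTES.
- **That OA1 performs the follow-up examinations.** This is an inference; the coordinators conduct the visits.
- **That counting only imaging-confirmed hernias, or grading by Clavien–Dindo, would solve the problem.** Imaging still follows suspicion, and grading measures severity. Neither equalises detection.

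**Conclusion.** The point holds on two counts. First, the physical examination for IH cannot be both routine at every visit and performed only as needed, and the passages must be reconciled. If the discretionary rule were followed, detection of incisional complications could differ between arms. This is a risk that follows from the text and the different incision sites; nothing in the documents shows that it would occur or which arm it would favour. Second, the assessor-blinding claim is wrong as written for the incision, because the described measures do not hide the incision site from its assessor beyond the dressings in hospital. The Discussion concedes the weakness for patients only.

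The scale is small in absolute terms and large relative to the expected yield: about 1.5 to 2.5 cases in the TU-LESS arm, with each case worth 2.8 to 3.4 percentage points. This rests on the article's 5–7% rate, 29 to 36 patients, and no assumption about vNOTES. The 1.25 to 3.5 point range for reduced detection rests on an assumed 50–75% relative detection and is illustrative only. The completion-of-surgery outcome is not affected.

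**What to change.** 1. In Postoperative follow-up, make the physical examination follow the rule already given under incisional complications: at every visit, the same examination of both the umbilical and the vaginal site in both arms. Keep the discretionary wording for ultrasound and other imaging only.
2. In Study design and in Data collection and management, limit the assessor-blinding claim to the non-incisional outcomes assessed by OA2, and state that assessment of the incision is unblinded.

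Both are changes of wording. The every-visit examination is already stated in the article, so the first change adds nothing to that section's plan beyond making explicit that both sites are examined in both arms. The price of the second is a weaker, but accurate, blinding claim.
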